**The Dietary Intervention**

**in *e*-shopping Trial**

# PROTOCOL

## AIMS

The primary aim of this randomised controlled trial is to investigate whether tailored dietary advice, delivered over the Internet during Internet shopping, is an effective means of achieving long-term modification of online food purchasing habits related to saturated fat. More specifically, the primary hypothesis is:

- That among users of an online grocery shopping facility, compared to control, provision of tailored dietary advice targeting saturated fat, will result in the purchase of foods with a lower average saturated fat content over a 6-month follow-up period.To determine the effects of real-time, tailored dietary advice, on the amount of saturated fat in purchases made by individuals using an Internet grocery shopping facility.

### EXPERIMENTAL DESIGN

- The Dietary Intervention in ‘e’-shopping Trial (DI*e*T) is a randomised controlled trial that will be conducted among 500 individuals that regularly use an established online grocery shopping facility. The trial will be conducted in collaboration with *shopfast.com* that already offers an online grocery shopping service.

### PARTICIPANTS & RECRUITMENT

- Consecutive individuals using the online shopping service will be offered the opportunity to participate in the trial until the study recruitment target of 500 is achieved.
- Individuals will be eligible to enroll in the study only once, and must be planning to use the online shopping facility at least once more within the following 6-month period.
- The option to participate will be given during a usual visit to the online shopping Website - after the items for purchase have been selected (‘baseline shopping list’) and just prior to entering the online ‘checkout’ process, a short on screen message will provide brief information about the study. Shoppers will be given the option either to continue through to the ‘checkout’ as usual, or to consider participating in the study.
- Participants that indicate interest in the study will immediately be provided with detailed information about the study while online and will be asked to provide informed consent to participate.
- Once consent is provided, simple baseline information will be collected by means of an online questionnaire, followed by immediate randomisation to either intervention or control.

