**EXCLUSION CRITERIA**

- Individuals who do not intend to use the online shopping facility again within the proceeding 6 months will be excluded from the study. This will be determined by the answer to question 1 in the online questionnaire.
- Any others??

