### RANDOMISATION, INTERVENTION AND CONTROL

Randomisation will be done by a central computer using minimization to achieve balance for key factors that might influence the response to the intervention (including: age, gender, baseline percentage of saturated fat in shopping list, number of individuals in household). The two groups will be:

1. Intervention group: individuals assigned to the intervention group will receive immediate, highly tailored advice about the items in the ‘baseline shopping list’ with the aim of reducing the amount of saturated fat purchased. This will be achieved by using a computer algorithm to identify the products that are high in saturated fat and then offering similar, but lower fat, alternatives. Summary information about the impact of selecting these alternatives on the saturated fat content of the shopping list will be provided and the participant will then be free to either purchase the alternatives or retain the original selections. They will then proceed with their modified shopping list (‘first follow-up shopping list’) and complete online ‘checkout’ as usual.
2. Control group: individuals assigned to the control group will receive immediate, general advice about how to choose a diet low in saturated fat and the health advantages this may confer. This information will be delivered via a traditional, static Web page. They will then proceed to online ‘checkout’ as usual.

All advice provided to the intervention and control groups will be in line with accepted Australian Heart Foundation recommendations, the difference between the groups being in the tailoring of the information provided.

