### DATA COLLECTION AND FOLLOW-UP

For each randomised participant, follow-up will comprise one or more post-randomisation visits to the online shopping site during the six-month period after randomisation. At the baseline visit a unique study identification number will be assigned and the following information will be collected and stored in the database:

- Participant demographics (age, gender, postcode, number of individuals in household)
- The first ‘baseline shopping list’ (i.e. the items selected for purchase prior to the provision of any dietary advice)

At each subsequent visit to the online shopping site the information collected and stored will be:

- The second (third, fourth… etc) ‘baseline shopping lists’ (i.e. the items selected for purchase prior to the provision of dietary advice at subsequent visits) and the second (third, fourth… etc) ‘follow-up shopping list’ (i.e. the items actually purchased after the prompt about dietary advice at subsequent visits).

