### PRIMARY OUTCOME

The primary outcome will be the difference between randomised groups in the mean percentage of saturated fat, in the shopping purchased online, during the 6-month follow-up period.

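### The once-only enrolment rule covers individuals but not households or shopping accounts, so members of one household can be randomised to opposite arms (minor)

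*Protocol*

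**What the plan says.** Under PARTICIPANTS & RECRUITMENT the Protocol states: "Consecutive individuals using the online shopping service will be offered the opportunity to participate in the trial". The only limit there on repeat entry is "Individuals will be eligible to enroll in the study only once".

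EXCLUSION CRITERIA fixes one exclusion, "Individuals who do not intend to use the online shopping facility again within the proceeding 6 months will be excluded from the study", and then closes with an open query about further criteria. It contains no household, account or delivery-address rule.

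Under RANDOMISATION, INTERVENTION AND CONTROL each individual is allocated by minimisation. The factors, described as ones that might affect response, include "baseline percentage of saturated fat in shopping list, number of individuals in household".

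On data, DATA COLLECTION AND FOLLOW-UP says: "At the baseline visit a unique study identification number will be assigned". It lists age, gender, postcode and household size, plus the shopping lists, including "the items actually purchased after the prompt about dietary advice at subsequent visits". It names no household or account identifier and does not say how a later visit is tied to a study ID.

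The PRIMARY OUTCOME is the between-group difference in the "mean percentage of saturated fat, in the shopping purchased online, during the 6-month follow-up period". STATISTICAL ANALYSIS compares the groups with unpaired t-tests.

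**The concern.** A second adult in an enrolled household is a different individual, so the rule as written admits that person and randomises them separately. The Protocol does not call the outcome household shopping, and its aims speak of individuals' purchases. But its use of household size as a factor that may affect response makes sense mainly if a list often feeds more than one person.

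If two members land in opposite arms, two things follow:

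- **Contamination.** Swaps accepted by the intervention member change what the household keeps and reorders, and so can change the control member's list. The contrast shrinks towards zero.
- **Dependence.** The two outcomes are correlated, while the unpaired t-test treats every participant as independent.

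This belongs in the protocol because it is an entry rule. With only postcode and household size recorded, co-enrolled members could not be identified reliably afterwards, so an analysis plan could not dependably repair it.

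**Working it through.** **Inputs.** From SAMPLE SIZE ESTIMATES: N = 500, SD = 5 percentage points, difference = 2 points, alpha = 0.01, power at least 95%. Assumed: equal allocation (250 per arm) and a two-sided test, since sidedness is not stated.

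**Step 1: reproduce the stated power.**

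- SE of the difference = 5 × √(2/250) = 0.447.
- Power ≈ Φ(2/0.447 − 2.576) = Φ(1.896) = 97.1%. The noncentral t gives 97.0%, and a one-sided test 98.4%.
- The N needed for 95% power is 446 two-sided or 396 one-sided. The stated figure holds.

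**Step 2: opposite-arm pairs.** Let h be the share of participants who have a household member in the other arm. As a worst case, assume those pairs show no between-arm difference. The expected difference becomes 2 × (1 − h). The Protocol gives no value for h, so a range is shown.

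| h | Difference (points) | Power, normal | Power, noncentral t |
|---|---|---|---|
| 0 | 2.00 | 97.1% | 97.0% |
| 2% | 1.96 | 96.5% | 96.3% |
| 5% | 1.90 | 95.3% | 95.1% |
| 10% | 1.80 | 92.6% | 92.4% |
| 20% | 1.60 | 84.2% | not run |

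The smallest difference detectable with 95% power is (2.576 + 1.645) × 0.447 = 1.888 points. The 95% promise therefore fails once h exceeds 1 − 1.888/2 = 5.6% (normal approximation).

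**Step 3: what those shares imply.** With roughly even allocation, about half of co-enrolled pairs fall in opposite arms. So h = 5% needs about 10% of participants to come from twice-enrolled households: 500 × 0.10 = 50 people, or 25 households.

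**Step 4: dependence.** Let g be the share of participants in same-arm pairs and ρ the within-pair correlation. The variance of the difference is (2 × SD²/n) × (1 + ρg − ρh), with n = 250. Same-arm pairs inflate it and opposite-arm pairs reduce it. If g and h are about equal, the two cancel. Taken alone at ρ = 1, same-arm pairs give an effective n of 250/(1 + g) per arm, and power for the full 2 points is 96.3% at g = 5% and 95.4% at g = 10%.

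**The case against.** The strongest reply is that the numbers hardly move. Power stays above 95% at h = 5%, the model already assumes the worst for each affected pair, and nothing in the Protocol suggests that co-enrolment would be common. The dependence also works in both directions and largely cancels under even allocation. The exclusion list is openly unfinished, so this can be read as one criterion still to be filled in. All of that stands, and it is why the point is minor. It does not close the gap: no rule keeps household members out of opposite arms.

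A reader might go further in two ways that the Protocol does not support:

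- **That the same purchases are counted in both arms.** Each participant has a unique study ID, and lists are stored at that participant's visits, so an order would normally count once. Double counting would need two IDs on one account. The Protocol is silent on that matching; it does not provide for it.
- **That minimisation steers the second member to the opposite arm.** Minimisation works on factor totals over everyone enrolled so far, and one earlier household member adds one count to them. Gender is also a factor and may differ. Any lean is negligible unless the two enrol almost back to back.

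**Conclusion.** The gap is real but minor. Entry is limited by individual only, so members of one household can be randomised to opposite arms, with bias towards no effect and some loss of independence. Under the worst-case assumption the expected difference falls by 0.1 point at h = 5% (2.0 to 1.9) and by 0.2 point at h = 10%, with power of about 95% and 92% to 93% against about 97% with no sharing. These figures rest on 250 per arm, a two-sided test, the Protocol's SD of 5 and an assumed h. How often co-enrolment would occur cannot be judged from the Protocol. That an online list commonly serves a household is an inference from the use of household size, not the Protocol's own wording. The stated sample size remains correct on its own assumptions.

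**What to change.** Change the entry rule to one enrolment per household. Check it by shopping account, or by a screening question in the baseline questionnaire, which already screens on intention to shop again. Do not show the study offer again to an enrolled account. State that later orders are matched to the study ID through the enrolled participant's account.

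Do not go as far as crediting every order from a delivery address to the first enrolment. That would bring in purchases by people who gave no consent, and unrelated people may share an address.

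The cost is one eligibility sentence, one check or question in software still to be built under the Protocol's timeline, and a few shoppers not offered the trial. The account route assumes that the retailer's system can recognise an enrolled account, which the Protocol does not state; the screening question does not depend on this. N = 500 and its power are unchanged.

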**EXCLUSION CRITERIA**

- Individuals who do not intend to use the online shopping facility again within the proceeding 6 months will be excluded from the study. This will be determined by the answer to question 1 in the online questionnaire.
- Any others??

### RANDOMISATION, INTERVENTION AND CONTROL

Randomisation will be done by a central computer using minimization to achieve balance for key factors that might influence the response to the intervention (including: age, gender, baseline percentage of saturated fat in shopping list, number of individuals in household). The two groups will be:

1. Intervention group: individuals assigned to the intervention group will receive immediate, highly tailored advice about the items in the ‘baseline shopping list’ with the aim of reducing the amount of saturated fat purchased. This will be achieved by using a computer algorithm to identify the products that are high in saturated fat and then offering similar, but lower fat, alternatives. Summary information about the impact of selecting these alternatives on the saturated fat content of the shopping list will be provided and the participant will then be free to either purchase the alternatives or retain the original selections. They will then proceed with their modified shopping list (‘first follow-up shopping list’) and complete online ‘checkout’ as usual.
2. Control group: individuals assigned to the control group will receive immediate, general advice about how to choose a diet low in saturated fat and the health advantages this may confer. This information will be delivered via a traditional, static Web page. They will then proceed to online ‘checkout’ as usual.

All advice provided to the intervention and control groups will be in line with accepted Australian Heart Foundation recommendations, the difference between the groups being in the tailoring of the information provided.

### DATA COLLECTION AND FOLLOW-UP

For each randomised participant, follow-up will comprise one or more post-randomisation visits to the online shopping site during the six-month period after randomisation. At the baseline visit a unique study identification number will be assigned and the following information will be collected and stored in the database:

- Participant demographics (age, gender, postcode, number of individuals in household)
- The first ‘baseline shopping list’ (i.e. the items selected for purchase prior to the provision of any dietary advice)

At each subsequent visit to the online shopping site the information collected and stored will be:

- The second (third, fourth… etc) ‘baseline shopping lists’ (i.e. the items selected for purchase prior to the provision of dietary advice at subsequent visits) and the second (third, fourth… etc) ‘follow-up shopping list’ (i.e. the items actually purchased after the prompt about dietary advice at subsequent visits).

### PRIMARY OUTCOME

The primary outcome will be the difference between randomised groups in the mean percentage of saturated fat, in the shopping purchased online, during the 6-month follow-up period.

### STATISTICAL ANALYSIS

The analyses will include all randomised participants and will be conducted according to the principle of ‘intention-to-treat’. For the primary outcome, comparisons will be made using unpaired t-tests. Exploration of the effects in participant groups and over time will be explored in an effort to better understand the effects of the intervention, but the emphasis will always be on the overall study result for the primary outcome.

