### SAMPLE SIZE ESTIMATES

The sample size of 500 has been selected to provide at least 95% power to detect a 2% or greater absolute difference in the mean saturated fat content of the follow-up shopping lists, between the intervention and control groups (with alpha=0.01). These estimates assume that the mean saturated fat content of the shopping purchased at baseline is between ten and fifteen percent and that the standard deviation about the percentage of saturated fat purchased is 5%. Although online internet shoppers are unlikely to be entirely representative of the general population and are probably more likely to purchase foods with a lower saturated fat content, this is unlikely to move the mean saturated fat content of the shopping list outside the range estimated or to importantly effect the estimate of the standard deviation used. The 2% effect estimate is deemed plausible on the basis of a previous study with similar aims, in which a 3% absolute reduction in purchased saturated fat was achieved using an in-store kiosk to provide computerised dietary advice to customers. The estimate is also compatible with the effects on saturated fat consumption observed in a number of other studies targeting dietary intake rather than food purchases.

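### The primary unpaired t-test ignores the baseline saturated fat used to balance the groups; if baseline predicts follow-up, its standard error is too large, a conservative loss of precision that ANCOVA would recover at no cost

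*Protocol*

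**What the plan says.** Protocol, Randomisation, Intervention and Control, on how participants are allocated: "Randomisation will be done by a central computer using minimization to achieve balance for key factors that might influence the response to the intervention". The factors named are "age, gender, baseline percentage of saturated fat in shopping list, number of individuals in household", introduced by the word including, so the list may not be complete.

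Protocol, Data Collection and Follow-up: age, gender and household size are stored for each randomised participant. So is the first baseline shopping list, defined as "the items selected for purchase prior to the provision of any dietary advice".

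Protocol, Primary Outcome: "The primary outcome will be the difference between randomised groups in the mean percentage of saturated fat, in the shopping purchased online", over the six months of follow-up. This is a follow-up value, not a change from baseline.

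Protocol, Statistical Analysis: "For the primary outcome, comparisons will be made using unpaired t-tests". No covariate is mentioned.

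Protocol, Sample Size Estimates: 500 participants, for "at least 95% power to detect a 2% or greater absolute difference", with alpha 0.01 and SD 5%. No correlation between baseline and follow-up is used.

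**The concern.** The t-test's variance formula treats the groups as if they had been formed by simple randomisation. Minimisation removes much of the chance imbalance in the factors it uses, one of which is the baseline value of the outcome itself. Where that factor predicts follow-up, the observed difference varies less from trial to trial than the t-test supposes. The variation balanced by design stays in the error term, so the confidence interval is too wide and the p-value too large.

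Two things are at stake. The first is calibration: a test run at 1% would have a true size below 1%. The second is precision: an adjusted analysis would report a narrower interval from the same 500 people, and would be more likely to detect an effect smaller than 2 points.

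**Working it through.** **Inputs.** From Sample Size Estimates: N = 500, difference 2 points, SD 5, alpha 0.01, power at least 95%. Assumed, because not stated: 1:1 allocation (250 per group), a two-sided test, and r, the correlation between baseline and follow-up percentage saturated fat, shown over a range.

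**Step 1. The plan's own figure.** SE = 5 × √(2/250) = 0.447. Power = Φ(2/0.447 − 2.576) = Φ(1.896) = 97.1% (97.0% with the noncentral t; 98.4% if one-sided). For exactly 95% power, 223 per group (446 in total) suffice. The claim of at least 95% is therefore correct.

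**Step 2. Adjusting for baseline.** Adjusted SE = 0.447 × √(1 − r²). The half-width of the 99% interval is 2.576 × SE. The true size of the nominal 1% t-test, in the limit of perfect balance on baseline, is 2Φ(−2.576/√(1 − r²)).

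| r | Adjusted SE | Reduction from 0.447 | 99% half-width (t-test 1.15) | True size of t-test, perfect balance |
|---|---|---|---|---|
| 0.2 | 0.438 | 2% | 1.13 | 0.86% |
| 0.3 | 0.427 | 5% | 1.10 | 0.69% |
| 0.5 | 0.387 | 13% | 1.00 | 0.29% |
| 0.7 | 0.319 | 29% | 0.82 | 0.03% |

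**Step 3. Power, t-test against adjusted analysis.** For a true difference d, the t-test under perfect balance has power Φ((d/0.447 − 2.576)/√(1 − r²)). The adjusted analysis has power Φ(d/adjusted SE − 2.576).

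| r | d = 2 | d = 1.5 | d = 1 |
|---|---|---|---|
| 0.2 | 97.4% v 97.7% | 79% v 80% | 36% v 38% |
| 0.3 | 97.7% v 98.3% | 79% v 83% | 36% v 41% |
| 0.5 | 98.6% v 99.5% | 82% v 90% | 35% v 50% |
| 0.7 | 99.6% v 99.99% | 86% v 98% | 32% v 71% |

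**Step 4. Imperfect balance.** Real minimisation works on categories and usually with a random element, so perfect balance is a limit. Two simulations used 500 participants, four factors and a biased coin of 0.8, with baseline cut into three bands (1,500 runs) or four bands (2,000 runs). The bands and the coin are assumptions; the protocol gives neither.

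- The mean t-test SE stayed at about 0.447, while the actual SD of the difference was 0.395 to 0.418 at r = 0.5 and 0.339 to 0.356 at r = 0.7.
- The true size of the nominal 1% t-test was 0.45% to 0.7% at r = 0.5, with no rejections in either simulation at r = 0.7. At r = 0.3 (four bands only) it was 0.8%.
- ANCOVA on baseline (four bands) had size 1.2%, 1.0% and 0.65% at r = 0.3, 0.5 and 0.7, compatible with 1% for 2,000 runs.
- With SDs of 0.418 and 0.356 in place of perfect balance, the t-test's power at 1.5 points is about 80% (r = 0.5) and 84% (r = 0.7), and at 1 point about 36% and 33%.

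**The case against.** The strongest reply is that nothing the protocol promises fails. The test and the sample size agree with each other: both are unadjusted and both use the raw SD. The stated power at 2 points is met whatever r may be. The error is in the safe direction, so a positive result from the t-test would stand. At 2 points the gain from adjustment is at most about one percentage point of power. All of this stands, and it settles the grade of the point.

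It is also fair that r is unknown. The predictor is a single shopping list and the outcome covers six months of purchases, so a low correlation cannot be excluded. At r = 0.2 the gain is 2%. That stands too, and makes the claim conditional.

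Four stronger readings are tempting, and the document does not support them:

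- *That the trial is underpowered or its type I error inflated.* Power is 97.1% on the plan's inputs, and the true size is below the nominal level, not above it.
- *That the baseline list is wasted.* It drives both the minimisation and the tailored advice; it is unused only in the primary test.
- *That the t-test is at fault over participants who never return.* That is a missing-data question, commonly left to the analysis plan. ANCOVA also needs a follow-up value and can adjust only for measured covariates.
- *That missing effects below 2 points is a design failure.* The trial was sized for 2 points or more; better power below that is a bonus.

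What the reply does not remove is the mismatch. The protocol names the test, so this is not a detail left open for an analysis plan. Its own reason for minimising is that these factors may influence response; if they do predict follow-up, the named test misstates its own precision.

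**Conclusion.** The point holds as a conditional one. If baseline and follow-up saturated fat are positively correlated, the planned t-test overstates its standard error and is conservative. Adjustment cuts the standard error by 2% to 29% over r = 0.2 to 0.7. Near r = 0 there is nothing to gain. These figures rest on SD 5, 250 per group and a linear baseline effect; r is an assumption throughout.

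Under minimisation the t-test's estimate already enjoys much of the gain in precision. The four-band simulation put its actual SD at 0.395 at r = 0.5, close to the ANCOVA standard error of 0.387. The unadjusted analysis simply does not report that gain. The estimate is unbiased, type I error is not inflated and the stated power is met, so this is a free improvement and not a must-fix.

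**What to change.** Replace the t-test sentence in Statistical Analysis with wording such as: *The primary comparison is the adjusted mean difference from a linear model (ANCOVA) of each participant's follow-up percentage saturated fat on randomised group, baseline percentage saturated fat (continuous) and all other factors used in the minimisation (age, gender, number in household and any others), with its confidence interval. An unpaired t-test is a supportive analysis.*

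Referring to all minimisation factors matters because the protocol's list is not stated to be complete.

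The cost is one sentence. The named covariates are already collected before randomisation, no extra participants are needed, and the sample size can stand. The change should be made before outcome data are seen, so that the choice of an adjusted analysis cannot look selective.
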